## Abstract

**Introduction:**

Digital health tools such as smartphones and wearable devices could improve psychological treatment outcomes in depression through more accurate and comprehensive measures of patient behaviour. However, in this emerging field, most studies are small and based on student populations outside of a clinical setting. The current study aims to determine the feasibility and acceptability of using smartphones and wearable devices to collect behavioural and clinical data in people undergoing therapy for depressive disorders and establish the extent to which they can be potentially useful biomarkers of depression and recovery after treatment.

**Methods and analysis:**

This is an observational, prospective cohort study of 65 people attending psychological therapy for depression in multiple London-based sites. It will collect continuous passive data from smartphone sensors and a Fitbit fitness tracker, and deliver questionnaires, speech tasks and cognitive assessments through smartphone-based apps. Objective data on sleep, physical activity, location, Bluetooth contact, smartphone use and heart rate will be gathered for 7 months, and compared with clinical and contextual data. A mixed methods design, including a qualitative interview of patient experiences, will be used to evaluate key feasibility indicators, digital phenotypes of depression and therapy prognosis. Patient and public involvement was sought for participant-facing documents and the study design of the current research proposal.

**Ethics and dissemination:**

Ethical approval has been obtained from the London Westminster Research Ethics Committee, and the Health Research Authority, Integrated Research Application System (project ID: 270918). Privacy and confidentiality will be guaranteed and the procedures for handling, processing, storage and destruction of the data will comply with the General Data Protection Regulation. Findings from this study will form part of a doctoral thesis, will be presented at national and international meetings or academic conferences and will generate manuscripts to be submitted to peer-reviewed journals.

**Trial registration number:**

https://doi.org/10.17605/OSF.IO/PMYTA

Strengths and limitations of this studyThe current mixed methods design to evaluate feasibility and acceptability will provide a deeper understanding of the associations between patterns of missing data across the different data collection methods and clinical state.Both passive sensing and active validated questionnaire-based data collection methods will be evaluated.A 7-month participant follow-up provides a picture of engagement in the longer term, compared with previous studies.For pragmatic reasons, the study uses a non-randomised, non-controlled design, which will limit conclusions about digital changes to treatment response.This study does not use devices that are validated for medical use, drawing instead from digital sensors in Android smartphones and a Fitbit fitness tracker, which have been previously used in mental health research.

## Introduction

Depression is a leading cause of disability worldwide,^1^ yet response to treatment is poor, with only 50%–60% of people recovering after 3 months of treatment.^2 3^ Mental health science relies almost exclusively on subjective self-report to diagnose mental illness and measure outcomes. Reliance is therefore placed on patients being able to accurately recall and communicate complex mood states during clinical interviews, which many patients find difficult.^4 5^ Depending on subjective methods introduces a vulnerability to recall biases^6^ which may worsen with increased severity.^7^

The use of digital tools within mental health has the potential to enhance traditional self-report measures by improving aspects of symptom tracking, illness management and treatment support. Remote measurement technologies (RMTs) such as smartphones and wearable devices can unobtrusively capture a more accurate picture of a patient’s clinical state in a continuous way, with far less burden to the user. Through embedded sensors, they can detect changes in behaviours associated with depressive symptomatology such as sleep,^8^ sociability,^9^ physical activity^10^ and speech.^11^ Detecting such changes in a person’s behaviour can provide invaluable information for tailoring and improving treatment.

Given the relative recency of the field, and with an eye towards clinical implementation, studies on RMTs and depression have largely comprised proof-of-concept, feasibility and acceptability studies. While studies show RMTs to be generally feasible and acceptable,^12^ the data predominantly come from small, non-clinical or student samples with a median follow-up time of 2 weeks.^13^

To our knowledge, no such feasibility studies have been published on the use of RMTs to track mood and behaviour in clinical populations undergoing psychotherapy for depression. This population could derive greater benefits from the application of such digital methods by alleviating distress in more potentially severe cases and reducing pressure on healthcare services. In addition to the barriers of adopting RMTs for mood monitoring found across populations, such as concerns around privacy, confidentiality, affordability and accessibility, there are likely to be additional considerations related to the help-seeking populations that remain unexplored and may help or hinder implementation practices in the future.

From a clinical perspective, exploring feasibility and acceptability in therapy populations can shed light on how changes in severity affect engagement with and use of digital devices, how they can be used to complement treatment and the barriers and facilitators to their use and implementation within services. From a methodological perspective, it would be important to establish the extent to which the amount and quality of data is usable and unbiased given that the added workload from therapy exercises, homework and clinical questionnaires as well as the severity of symptoms such as decreased motivation and cognitive abilities are likely to affect engagement and device use.^12^ Such studies could also inform future projects about the likely uptake in these samples in order to establish sample sizes and allocate resources.

### Study aims

The primary aim of this project is to evaluate the extent to which data collection with digital tools on clinical samples is feasible. Specifically, the feasibility of using RMTs, such as Android smartphones and a Fitbit wearable device, to collect behavioural and clinical data in people undergoing therapy for depressive disorders, to establish the extent to which they can be potentially useful biomarkers of depression and changes in clinical state. The purpose of this is to describe patterns of user engagement and missing data, which are likely to impact the scientific integrity of future large-scale studies.

Secondary aims are to identify candidate signals for digital biomarkers by detecting correlations between objective features and clinical characteristics, and to explore whether these signals have prognostic value in the context of psychological treatments.

## Methods and analysis

### Design

This is an observational, prospective cohort study of people attending psychological therapy for depression. It will use RMTs to gather active and passive data for up to 7 months and will adopt a mixed methods design to evaluate the feasibility and acceptability of such data collection methods.

### Setting

Participants will be drawn from Improving Access to Psychological Therapies (IAPT) services in South London. The participating IAPT services will be from the boroughs of Lambeth, Lewisham and Croydon within the South London and Maudsley NHS Foundation Trust. IAPT is a publicly funded self-referral outpatient programme providing evidence-based psychological treatments for adults with mild-to- moderate mental health disorders. The service is free at the point of delivery.

Recruitment for this study initiated in June 2020 during the COVID-19 pandemic. Given the government-imposed travel restrictions and social distancing measures, the entirety of this study will be carried out remotely.

### Sample size

Formal sample size calculations are not a requirement for feasibility studies^14^; however, the general recommendation is for samples of 50–60 participants to assess feasibility outcomes.^15^ In order to address our secondary aims, a sample size of 50 would be sufficiently powered to detect a correlation coefficient of 0.39 and above, assuming a significance level of 0.05 and type 2 error value of 0.20. Based on previous studies, we expect such an effect size.^16–18^ To account for a potential attrition rate of 20% we will aim to recruit 65 participants.

### Recruitment

IAPT clinicians will act as gatekeepers to the initial recruitment process. Patients within their service, who have previously agreed to be contacted for research purposes, will be invited to take part, either by phone call or email. They will be given a summary of the aims and procedures of the study and be screened for eligibility as per the inclusion/exclusion criteria below. When screening is done by email, participants receive a personalised email with a description of the study and a link to an online screening tool that participants can complete in their own time, the responses of which are relayed to the research team. If willing and eligible, potential participants will be sent the participant information sheet and given at least 24 hours before going through the consent procedures and being enrolled in the study.

#### Inclusion criteria

Adults with a current depressive episode as measured by the Mini International Neuropsychiatric Interview (MINI^19^).Being on the waiting list to receive treatment for depression at IAPT services, with an expected wait of at least 7 days (to a maximum of 5 weeks) between scheduled enrolment and first treatment session. Due to the prevalent comorbidity with anxiety disorders, people with a main diagnosis of anxiety were also included, provided they met inclusion criterion A.Existing ownership of Android smartphone with sufficient memory space for the relevant apps.Able and willing to use a wrist-worn device for duration of the study.Able to give informed consent for participation.Sufficient English language skills to understand consent process and questionnaires.

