#### Secondary outcomes

Secondary outcomes will evaluate the relationship between digital data and clinical outcome measures, both at individual time points and as prognostic factors for recovery after treatment. Scores on clinical scales will be used in addition to individual symptom domains.

Digital outcomes will be derived from smartphone and Fitbit sensors, and digital features from passive measures described in the ‘Passive Measures’ section, such as GPS signal patterns, sleep, phone use and Bluetooth interactions. They will be extracted to form averages that encapsulate daily, weekly and within-treatment means and SDs or frequency counts.

Clinical state will be measured using:

Patient Health Questionnaire (PHQ-9)^30^: the nine-item questionnaire that is widely used for measuring depression in IAPT services.Generalized Anxiety Disorder^31^ questionnaire: will be measured as it gathers important anxiety symptoms which are so often comorbid with depression.Quick Inventory of Depressive Symptomatology-Self-Report (QIDS-SR)^32^: this is a 16-item inventory of depression for patients who identify as depressed or who may be suffering from depression.Work and Social Adjustment Scale^33^: a measure of quality of life/disability, which is a five-item assessment of perceived social and work-related functional impairment used widely across a range of mental and physical disorders.Cognition via the THINC-it app.

Participants will be considered to be in remission if they have experienced a reduction of at least 50% in depressive symptomatology from the start of treatment, or no longer meet criteria for depression according to the PHQ-9 (scoring below the cut-off of 5). Subdimensions of depression—for example, interest in activities, motivation, appetite—will be gathered from the QIDS-SR.

The sociodemographic, clinical and contextual variables measured, such as illness severity, cognitive function and social support, will be taken as covariates.

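### The PHQ-9-below-5 limb of remission has no dated starting point, so a participant already below 5 at the first session and still below 5 at assessment counts as remitted without improving during treatment

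*Protocol article*

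**What the plan says.** **Entry** (Protocol article, Inclusion criteria). Depression is established by interview: "Adults with a current depressive episode as measured by the Mini International Neuropsychiatric Interview". Neither the inclusion nor the exclusion list sets a PHQ-9 minimum. Participants must be on the waiting list "with an expected wait of at least 7 days (to a maximum of 5 weeks) between scheduled enrolment and first treatment session". A main diagnosis of anxiety is allowed on a condition: "people with a main diagnosis of anxiety were also included, provided they met inclusion criterion A".

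**Schedule** (Table 1). The MINI is given at enrolment only. PHQ-9 is collected at enrolment, fortnightly and at endpoint, and QIDS-SR at enrolment and weekly. Endpoint assessment is 12 weeks after treatment ends (End of study).

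**Remission** (Secondary outcomes). There are two alternative limbs. The first is "a reduction of at least 50% in depressive symptomatology from the start of treatment". The second is "or no longer meet criteria for depression according to the PHQ-9 (scoring below the cut-off of 5", with no starting score or date attached.

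**Use** (Secondary outcomes). Digital data are to be related to clinical outcomes "both at individual time points and as prognostic factors for recovery after treatment".

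**The concern.** The two limbs start from different places. The first compares a later score with the score when therapy began. The second looks at the later score and, through its wording, at some undated earlier state. Depression status is fixed by a different instrument, up to five weeks before therapy, and no re-check at the first session is described.

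A person below 5 when therapy starts cannot recover during therapy in the PHQ-9 sense, because that person is not at risk of the event. If still below 5 at assessment, the person joins the remitted group, and does so with one of the lowest starting scores in the cohort. Any digital feature that reflects severity at the start of therapy can then look prognostic when it is only detecting existing status. The remission proportion also rises. In a cohort of about 50, a few such people form a noticeable part of the remitted group.

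**Working it through.** **1. The denominator.** The article's sample of 50 reproduces. By Fisher's z with two-sided alpha 0.05 and power 0.80, n = ((1.960 + 0.842)/atanh(0.39))² + 3 = (2.802/0.412)² + 3 = 49.3, rounded up to 50. Allowing for 20% attrition, 50/0.8 = 62.5, rounded up to 63, and the target of 65 covers this. The point below does not depend on these figures; 50 serves only as the denominator.

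**2. What the rule classifies.** Assume both limbs are scored on PHQ-9 with a range of 0 to 27 (the article states neither). Take the below-5 limb as a condition on the final score only, and consider every pair of start-of-treatment and final scores.
- Remitted with an unchanged score: 0-0, 1-1, 2-2, 3-3 and 4-4, so 5 pairs.
- Remitted with a worse score: any rise within 0 to 4, such as 0 to 4, so 5 × 4/2 = 10 pairs.
- If a start score of 5 or more is required: none. A final score below 5, or at most half the start score, is then always a fall.

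**3. What the words "no longer meet criteria for depression according to the PHQ-9 (scoring below the cut-off of 5" add.** They imply that the criteria were met at some earlier time. There are two candidates for that time.
- Start of treatment: the gap closes, but the text does not say this.
- Enrolment: a participant at 5 or more then, below 5 at the first session and below 5 at assessment satisfies the wording, with no change during therapy.

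The wording therefore narrows the gap without closing it.

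**4. How many people.** The article gives no PHQ-9 mean, SD or waiting-list change, so everything here is assumption: enrolment mean 13 to 16, SD 4.5 to 5, mean change over the wait −1 to −1.5, and the SD at the start of treatment equal to that at enrolment. By normal approximation, P(score < 5) = Φ((4.5 − mean at start)/SD):
- mean 16, SD 4.5, change −1: Φ((4.5 − 15)/4.5) = Φ(−2.33) = 1.0%, or 0.5 of 50
- mean 14.5, SD 4.5, change −1: Φ(−2.00) = 2.3%, or 1.1 of 50
- mean 14.5, SD 4.5, change −1.5: Φ(−1.89) = 2.9%, or 1.5 of 50
- mean 13, SD 5, change −1: Φ(−1.50) = 6.7%, or 3.3 of 50
- mean 13, SD 5, change −1.5: Φ((4.5 − 11.5)/5) = Φ(−1.40) = 8.1%, or 4.0 of 50

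Zero is also possible, so the working range is 0% to 8%.

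**5. Effect on the remission figures at the upper end.** Let q = 0.08 be below 5 at the start and all stay there. Let the others remit at r = 0.5 or 0.6, borrowing the 50%–60% recovery figure in the Introduction for illustration. The observed rate is q + (1 − q)r.
- r = 0.5: 0.08 + 0.92 × 0.5 = 0.540, a rise of 4.0 points; share of remitters 0.08/0.540 = 14.8%
- r = 0.6: 0.08 + 0.92 × 0.6 = 0.632, a rise of 3.2 points; share of remitters 0.08/0.632 = 12.7%

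If some rise to 5 or above by assessment, these figures fall.

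**The case against.** The case against giving this much weight has several sound parts.

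- **Wording.** A reader might infer that the below-5 limb has no starting requirement at all. It does imply an earlier positive state. Someone who scored low on PHQ-9 throughout never met the criteria, so does not fit the wording. What remains is that the earlier state is undated.
- **Persistence.** A reader might infer that anyone below 5 at the first session becomes a success automatically. They must also be below 5 when remission is assessed, and the endpoint is 12 weeks after treatment ends. Those who fell below 5 on the waiting list have also changed since enrolment, though not during therapy.
- **Anxiety entrants.** It is tempting to see them as a source of low PHQ-9 scores. They too must have a current depressive episode on the MINI, and nothing in the article suggests that they score low.
- **Detectability.** These people are not hidden. The scheduled PHQ-9 and QIDS-SR forms can identify them, although the remission rule does not use the forms to do so.
- **Size.** Adding an assumed change SD of 3 to 4 to the enrolment variance gives 2.6% to 13.7%. That is too wide: in the top case the SD grows from 5 to √(25 + 16) = 6.4, and about 3.0 of the 13.7 percentage points are impossible negative scores.
- **Consequence.** Illness severity is listed as a covariate, the machine learning work is conditional on sufficient data, and the sensitivity and specificity sentence names relapse, not remission. The primary outcomes are descriptive and unaffected.
- **Detail left elsewhere.** The at-risk set of an exploratory analysis is often left to the analysis plan. Here, however, the article states the remission rule itself, with its cut-off and with an anchor for one limb only. The point concerns that rule as written.

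These arguments reduce the point to a modest one. They do not supply the missing anchor.

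**Conclusion.** The point holds in a limited form. As written, the remission rule can class a participant as remitted with no improvement during treatment if the PHQ-9 is below 5 both at the first session and at assessment. This follows from the text: interview-based entry with no PHQ-9 minimum, a wait of up to 5 weeks, and one limb of the rule without a date.

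The number affected cannot be derived from the documents. An assumed 0% to 8%, or 0 to 4 of 50, is a reasonable range. It rests on the assumed means and SDs and on an unchanged SD over the wait; the effect on the remission rate also assumes that everyone affected stays below 5. The documents do not support a claim that the remission results are seriously inflated or that the prognostic analysis is invalid. Feasibility outcomes, continuous-score analyses and the sample size are untouched. This is an inexpensive improvement to a secondary analysis.

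**What to change.** In Secondary outcomes, add wording to this effect: both limbs of remission are judged against the last PHQ-9 completed before the first treatment session; the remission and prognostic analyses include participants scoring 5 or more on that form; those already below 5 are counted and described separately; everyone stays in the feasibility and continuous-score analyses.

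**Cost.** A sentence or two of analysis wording, with no new data collection because PHQ-9 is already scheduled fortnightly. A few participants leave the remission analysis.

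**Limit.** With a short wait, the last PHQ-9 before therapy may be the enrolment score. If the first fortnightly form falls 14 days after enrolment, this applies to waits of 7 to 13 days. Some waiting-list improvement will then go undetected, so the time between that form and the first session should be reported.

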#### Exclusion criteria

Lifetime diagnosis of bipolar disorder, schizophrenia and schizoaffective disorders as these have different digital patterns to depression.^20 21^Health anxieties that may significantly worsen with constant monitoring of behaviour.Extensive sharing of smartphone with friends or family.Night shifts, pregnancy or living with a baby aged 0–6 months (due to sleep disruptions).

### Study procedures

Once interest and eligibility have been ascertained, participants will be invited to attend an enrolment session via video call. Figure 1 shows the study timeline for participants as they enter the study. After a further review of study procedures and opportunity for questions, participants will be asked to sign an electronic consent form. Consent can be taken either using the Qualtrics platform, which has been approved for this purpose, or via MS Word or PDF documents which participants electronically sign from their devices.

**Figure 1 F1:**
[figure not shown]
Study timeline for participants.

#### Enrolment/baseline

Following consent, the enrolment session comprised three further sections: (1) obtaining sociodemographic and clinical data, (2) completion of self-reported questionnaires, and (3) technology set-up. The researchers will take demographic and clinical information related to current and previous physical and mental health conditions, family history, treatment status as well as phone use, previous experience with health apps and devices and social and physical activity levels. In order to detect the presence of a depressive episode, and define whether atypical in nature, MINI and the Atypical Depression Diagnostic Scale^22^ will be administered. At the end of the session, participants will be asked to complete a battery of self-reported questionnaires as shown in table 1.

**Table 1 T1:** Schedule of events

Event	Enrolment	Questionnaire frequency			
		Weekly	Fortnightly	Monthly	Endpoint
Informed consent	x				
Sociodemographic data	x				
Clinical history	x				
MINI	x				
ADDS	x				
Smartphone apps set-up	x				
**Active measures*** **(from REDCap)**					
*Validated questionnaires*					
SAPAS	x				
BIPQ	x				x
Life stress (SRRS)	x				x
CTQ	x				
AUDIT	x				
PHQ–9	x		x		x
GAD-7	x		x		x
Rumination (RRS)	x			x	
AUDIT (short version)	x		x		
Oslo 3-item Social Support Scale	x			x	
Perceived Stress Scale	x			x	x
WAI-SR†					x
*Contextual information*					
Caffeine intake	x	x			
Treatment status and content‡	x	x			
Social activities	x		x		
Social distancing practices	x		x		
COVID-19 experience	x			x	
